#### Objective 3: determination of treatment effects in an understudied disease stage

We will select separate cohorts of patients who have a valid COPD diagnosis in the CPRD^8^ and who would not have been eligible for inclusion in the TORCH trial (or our objective 1) due to the following characteristics: (1) >60% predicted FEV_1_ (or >50% plus Medical Research Council breathlessness scale 1 or 2, or >50% plus COPD Assessment Test score <10) and (2) no exacerbations in the year post-COPD diagnosis. We will also perform a sensitivity analysis where we allow the group of people with FEV_1_ >60% predicted who had a maximum of one exacerbation within 1 year post-COPD diagnosis to be included. As for objective 2, the selection steps will be similar to objective 1, with modified criteria for step 1 and the removal of the TORCH-matching step (step 3).

### Exposures, outcomes and covariates

#### Exposures

For all objectives, exposures will be determined using CPRD prescribing records and code lists for COPD treatments (codelists provided in online supplementary material).

For objective 1, use of FP/SAL (trade name Seretide) is the primary exposure of interest and will be compared with no treatment with FP/SAL. We will limit included patients to those receiving Seretide 500/50, the dose used in TORCH. This information is recorded for all prescriptions of Seretide and this dose is the only currently approved dose for COPD in the UK (although we recognise some prescribing may not follow the licensed indication). If the results for our FP/SAL versus no treatment comparison are not consistent with the TORCH FP/SAL versus placebo results (see the ’Statistical analysis' and ’Validation of results against TORCH' sections for a definition of consistent), we will perform additional analyses where instead of using a no-treatment comparator group, our objective 1 comparator group will be people exposed to SAL, one of the other comparator groups from the TORCH trial.

As a secondary analysis in objective 1, other treatments for COPD will also be compared with no treatment. Selection of unexposed and exposed people for each of these drugs will follow steps 1–6 detailed above in the ’Selection of participants—objective 1' section, although step 3 will be omitted (as these cohorts will not need to be matched to TORCH). The other treatments we plan to include are as follows:LABALAMALABA+LAMA LABA+ICS other than FP/SALLABA+LAMA+ICS.

For objectives 2 and 3, we will again use recorded prescribing information to determine the dose received. We will be reliant mostly on the strength of each individual drug, which is recorded automatically against each product and does not require general practitioners (GPs) to enter these data, ensuring completeness. We will then be able to stratify analyses based on the dose prescribed. Specific exposures for objectives 2 and 3 are as follows (all vs no treatment):FP/SALLABALAMALABA+LAMA LABA+ICS LABA+LAMA+ICS.

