### TORCH

TORCH was a placebo-controlled randomised trial of the combined inhaler FP/SAL for the treatment of COPD, published in 2007. Patients were randomised to receive FP/SAL, FP alone, SAL alone or placebo and the primary comparison of interest was between FP/SAL and placebo.^2^ Key outcomes were expected benefits (rate of COPD exacerbation and mortality) and an expected harm due to the immunosuppressive action of the corticosteroid FP (pneumonia). While findings for the primary end point of mortality were null, this was thought to be due to poor statistical power as a result of a lower than anticipated mortality rate. Nonetheless, a lower rate of exacerbations was seen with FP/SAL, and a higher rate of pneumonia was observed. As one of the largest trials in COPD, and with 3-year follow-up, TORCH is a landmark study, providing a validation point for our study. We will obtain individual patient data from the TORCH study via www.clinicalstudydatarequest.com for use in objective 1 (see the ’Selection of participants' section).

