**Figure 2 F2:**
[figure not shown]
Flow chart illustrating the planned selection of CPRD participants for objective 1 of the COPD real-world medicines effects study. Note in relation to step 5 (n~18 000) compared with step 1 (n~13 000): approximately 90% of the treated patients will also have been eligible as untreated patients, as they did not receive FP/SAL on their TORCH-eligibility date. This means that they will have at least one period of time during which they are untreated-eligible but then did subsequently go on to receive FP/SAL (meaning they have at least one period of time during which they are treated-eligible). If a person is included as both a treated and untreated participant, they will be contributing different periods of their person-time to each cohort (pre-FP/SAL treatment for the untreated vs post-FP/SAL treatment for treated), and this is handled in the analysis by assigning different index dates. COPD, chronic obstructive pulmonary disease; CPRD, UK Clinical Practice Research Datalink; FP/SAL, fluticasone propionate+salmeterol.

##### Step 1

We will select all patients in the CPRD with COPD who are eligible for HES-linkage and during the period covered by the linkage would have met the following TORCH study inclusion criteria:a diagnosis of COPD;age 40–80 years;smoking history;lung function (forced expiratory volume in 1 s (FEV_1_) <60% predicted, FEV_1_/forced vital capacity (FVC) ratio <70%).

An eligible-for-inclusion date will then be assigned as the date that all of the above inclusion criteria were met for the individual. We will then exclude any individual who has any of the following TORCH study exclusion criteria prior to their eligible-for-inclusion date:a diagnosis of asthma (within the previous 5 years);a diagnosis for any (non-COPD) respiratory disorder;a record of lung surgery;a diagnosis of alpha-1 antitrypsin deficiency;evidence of drug or alcohol abuse;a record of having received long-term oxygen therapy;diagnoses for conditions likely to interfere with the TORCH trial or cause death within 3 years;current use of oral corticosteroid therapy (defined as continuous use for >6 weeks, with courses of oral corticosteroids separated by a period of <7 days considered as continuous use);any exposure to FP/SAL within the previous 4 weeks.

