Finally, in-line with the TORCH trial approach, anyone who has an exacerbation requiring oral corticosteroid therapy or hospitalisation during the run-in period (the 2-week period following eligibility) will also be excluded.

Feasibility counts in the CPRD indicate there are ~13 000 patients meeting these criteria (figure 2). Given the limited information on how asthma exclusions were applied in the TORCH study, we will perform a sensitivity analysis in which the asthma exclusion is a diagnosis within the previous 1 year, rather than 5 years as specified above.

##### Step 2

Next we will determine if/when these patients ever received FP/SAL. During any time between attaining TORCH eligibility and a subsequent prescription for FP/SAL, patients will be eligible for inclusion as an unexposed (to FP/SAL) patient in objective 1. There may be multiple time periods within a person’s record where eligibility as an unexposed patient is met (figure 3). Feasibility work shows that between 1 January 2004 and 1 January 2017 there were ~11 000 TORCH-eligible patients in CPRD who did not receive FP/SAL at the time they attained TORCH eligibility and therefore have at least one time period that means they are eligible for inclusion as an objective 1 unexposed participant (figure 2). Individuals in CPRD who have more than one unexposed eligibility period within their record (figure 3) will be able to contribute more than once to the pool of unexposed participants (with the covariates and person-time contributed unique to the specific unexposed eligibility period).

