Having obtained individual-level patient data for TORCH participants from clinicalstudydatarequest.com, we will then match each TORCH participant (n=6112) 1:1 with the closest available unexposed patient record in the CPRD pool of FP/SAL untreated patients obtained in step 2. Matching will be based on the following TORCH baseline characteristics:agesexbody mass indexprevious treatment with:inhaled corticosteroidsLABA
history of COPD exacerbationshistory of cardiovascular diseaselung function.

Where an individual from CPRD has multiple unexposed ‘eligibility periods’ that can be matched to a TORCH participant, the CPRD characteristics that will be matched on will be those from the beginning of the specific eligibility period.

Some of the TORCH inclusion criteria will not be fully assessable using CPRD data (eg, we will be able to assess whether patients are smokers but will not always know their pack year history). Hence, the inclusion/exclusion criteria are analogous with TORCH criteria but we acknowledge they are not identical. Identification of criteria will be done based on algorithms already determined and by the identification of clinical codes in the CPRD. For those individuals that have contributed multiple unexposed records to the pool of CPRD unexposed participants (figure 3), after one of their unexposed records has been matched to a TORCH participant we will remove all of their other unexposed records (meaning that an individual can only appear once in the final TORCH-matched unexposed cohort). We anticipate matching all or the majority of TORCH participants with a CPRD patient, giving us a pool of TORCH-analogous untreated patients within CPRD, with similar baseline characteristics as TORCH participants at the point of randomisation (n~6000, figure 2).

##### Step 4

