#### Methods of analysis

For all objectives, comparisons will be made according to FP/SAL (or other drugs being analysed as specified in the ’Exposures' section) status for rate of COPD exacerbation, pneumonia and mortality over 3 years. All analyses will be performed according to the ‘intention-to-treat’ principle (as was done in the TORCH study), meaning that if a participant enters the study as either an exposed or unexposed participant, they will remain assigned to that exposure category for the entire duration of their follow-up (irrespective as to whether their true exposure status changes). For exacerbations, a negative binomial model will be used, accounting for variability between patients in the number and frequency of exacerbations, with the number of exacerbations as the outcome and the log of treated time as an offset variable. Time to mortality, first pneumonia and treatment change will be analysed using Cox proportional hazards regression. This mirrors TORCH end points of major benefit and harm. We anticipate the propensity matching process will allow us to assemble treated and untreated groups that are very similar with respect to baseline characteristics except FP/SAL treatment status. However, this will be tested by assessing standardised differences for each baseline variable. If substantial differences are noted for important variables, it may be necessary to further adjust the statistical models. This could also include examining the effect of using greedy versus optimum matching approaches in order to obtain the closest propensity score match and/or matching at a ratio other than 1:1.^17^

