#### Validation of results against TORCH

We will validate our findings against TORCH as part of objective 1 by determining whether results of the CPRD FP/SAL versus no FP/SAL treatment analysis are compatible with the TORCH exacerbations rate ratio for FP/SAL versus placebo (0.75; 95% CI 0.69 to 0.81). This outcome has been selected as it is an outcome of key significance for people with COPD^4^ and the result in TORCH shows a clear benefit with 95% confidence limits below 1. We have set two criteria that must be met for us to conclude results are consistent. First, the effect size must be clinically comparable with TORCH findings; the rate ratio for exacerbations in CPRD must be between 0.65 and 0.9. This range is deliberately not symmetrical around the TORCH estimate of 0.75 as we would anticipate the treatment effect in routine clinical care may be weaker than that seen in the optimised setting of a randomised trial. We recognise this rule could be met with a poorly powered, inconclusive result, so a second criterion is that the 95% CI for the rate ratio must exclude 1. If we go on to compare FP/SAL with SAL alone (see the ’Exposures, outcomes and covariates' section, ’Exposures' subheading), the 95% CI would also need to exclude 1, and the rate ratio would need to be between 0.81 and 0.95 (compared with the TORCH FP/SAL vs SAL result of 0.88, 95% CI 0.81 to 0.95).

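### The objective 1 comparator is defined only by absence of FP/SAL, so a partly active-controlled contrast can be accepted as reproducing the TORCH placebo result

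*Protocol article*

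**What the plan says.** All places are in the Protocol article.

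- **TORCH:** "Patients were randomised to receive FP/SAL, FP alone, SAL alone or placebo", with FP/SAL against placebo as the primary comparison.
- **Objective 1, Step 1:** the only exclusion for inhaled treatment is "any exposure to FP/SAL within the previous 4 weeks". Long-term oral corticosteroid use is also excluded. Current LABA, ICS, LAMA or another LABA+ICS is not.
- **Objective 1, Step 2:** at any time "between attaining TORCH eligibility and a subsequent prescription for FP/SAL, patients will be eligible for inclusion as an unexposed (to FP/SAL) patient".
- **Objective 1, Step 3:** "Matching will be based on the following TORCH baseline characteristics"; the list includes previous ICS and previous LABA, as matching variables and not as exclusions.
- **Exposures:** FP/SAL "will be compared with no treatment with FP/SAL". The fallback to a SAL comparator, used only if the first result is inconsistent with TORCH, is described as applying "instead of using a no-treatment comparator group". The section also lists LABA, LAMA, other LABA+ICS and triple therapy as regimens to be studied in CPRD, and describes the objective 2 and 3 comparisons as being against no treatment.
- **Covariates:** earlier treatment with other COPD drugs is a candidate for the propensity score.
- **Methods of analysis:** whatever happens later, "they will remain assigned to that exposure category for the entire duration of their follow-up".
- **Validation of results against TORCH:** the benchmark is the "TORCH exacerbations rate ratio for FP/SAL versus placebo (0.75; 95% CI 0.69 to 0.81"). The CPRD ratio must lie between 0.65 and 0.9 with a 95% CI that excludes 1.

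**The concern.** People not on FP/SAL and people on no treatment are different groups, and the protocol uses the two descriptions for the same comparator. As the selection rules stand, a patient taking another LABA+ICS on the index date is an eligible control.

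Matching and propensity scoring on previous treatment do not remove this. They balance drug history up to the index date. After it, the exposed patient starts FP/SAL while the matched control may simply continue the other inhaler. For such pairs the contrast is drug against drug, however well the baseline variables balance.

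Objective 1 is the in-built validation on which objectives 2 and 3 rest. If the comparator is partly active, agreement with a placebo-controlled ratio does not show what the protocol says it shows, and the acceptance rule has no means of telling the two situations apart.

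**Working it through.** The protocol's sample-size figure of 408 per group reproduces with a two-sided, continuity-corrected two-proportion formula (0.5 against 0.4, 80% power, 5%). It has no bearing here. The protocol gives no figure for treatment among controls, so the check shows a range.

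**Inputs from the protocol.** FP/SAL versus placebo 0.75; FP/SAL versus SAL 0.88; acceptance range 0.65 to 0.9; rate 0.5 per patient-year; about 6,000 per group; about 11,000 people in the unexposed pool; 6,112 TORCH participants.

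**Assumptions.** The true ratio against no treatment is 0.75. Other LABA+ICS has the same effect as FP/SAL (0.75). A LABA alone acts like SAL, for which the TORCH ratios imply 0.75/0.88 = 0.852 against placebo. Let p be the share of controls on another LABA+ICS and q the share on a LABA alone.

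**1. Expected ratio.** RR = 0.75 / [(1 − p − q) + 0.75p + 0.852q]

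| p | q | Expected RR |
|---|---|---|
| 0 | 0 | 0.75 |
| 30% | 0 | 0.75/0.925 = 0.81 |
| 50% | 0 | 0.75/0.875 = 0.86 |
| 67% | 0 | 0.75/0.833 = 0.90 |
| 0 | 50% | 0.75/0.926 = 0.81 |
| 0 | 100% | 0.75/0.852 = 0.88 |
| 30% | 30% | 0.75/0.881 = 0.85 |
| 50% | 30% | 0.75/0.831 = 0.90 |

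The ratio reaches the upper TORCH confidence limit (0.81) at about 30% on LABA+ICS or about 50% on LABA alone. LABA alone cannot take it past 0.88.

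**2. Can the acceptance rule detect this?** Take the extreme case in which every control is on a SAL-like drug. The expected ratio is 0.88, inside 0.65 to 0.9. Control rate 0.5 × 0.852 = 0.426, treated rate 0.5 × 0.75 = 0.375, negative binomial dispersion 1 (assumed):

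- One year: SE of log RR = √[(1/0.426 + 1/0.375 + 2)/6000] = 0.034; 95% CI around 0.88 is 0.82 to 0.94.
- Three years: SE = √[(1/1.278 + 1/1.125 + 2)/6000] = 0.025; 95% CI 0.84 to 0.92.

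Both intervals exclude 1. The estimate falls below 0.9 with probability Φ(ln(0.9/0.88)/SE), about 0.74 and 0.82. So a comparator with nobody untreated would be declared consistent with the placebo result about three times in four or more.

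**3. If the effect in routine care is weaker.** With a true ratio of 0.85 against no treatment (assumed), and other LABA+ICS equally effective, the share that brings the ratio to 0.9 is (1 − 0.85/0.9)/(1 − 0.85) = 37%.

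**4. Room to restrict the pool.** (11,000 − 6,112)/11,000 = 44%. This is an upper bound on the loss before 1:1 matching is incomplete; match quality would suffer sooner.

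**The case against.** Several counter-arguments have force.

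- **The size is unknown.** No share of controls on other inhalers is given, so the shift could be small. This stands; the figures above are a range.
- **Safeguards exist.** The acceptance range is deliberately wider on the side of a weaker effect, and an inconsistent result leads to a SAL comparison with its own range (0.81 to 0.95). This stands against any claim that dilution would simply end in failure. It does not help with a misleading pass: the wider range is justified by weaker effects in routine care, not by active controls, and the fallback starts only after an inconsistent result. The conditional sensitivity analyses cover adherence, leftover FP/SAL and the exacerbation definition, not controls' other inhalers.
- **Making the restricted group the primary comparator is a trade-off.** If 67% of the pool were on LABA+ICS, about 11,000 × 0.333 ≈ 3,670 people would remain for 6,112 matches; with 80% on active drugs, 2,200. At the 44% loss that the pool can bear, the expected ratio is 0.75/(0.56 + 0.33) = 0.84, well inside the range. Restriction is therefore easiest where the 0.9 limit is not threatened. TORCH participants with earlier ICS or LABA use could be matched only to people who had stopped those drugs, a selected group. Nor does a look-back at index deal with drugs started later. All this stands, and argues for a second analysis instead of a replacement.

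Two further inferences are tempting and not supported. A reader might suppose that TORCH participants had their previous ICS or LABA withdrawn at entry; the protocol gives only the four arms, and the point does not need it. A reader might also conclude that the same comparator passes unchanged into objectives 2 and 3. The text is mixed: the selection steps reuse objective 1 and refer to FP/SAL-unexposed periods, while the exposure list says no treatment. That calls for reconciliation and does not establish carry-over.

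**Conclusion.** The point holds. The objective 1 comparator excludes only FP/SAL, is also described as untreated, and is validated against a placebo-controlled ratio. Under the stated assumptions, 30% to 50% of controls on another LABA+ICS moves the expected ratio from 0.75 to between 0.81 and 0.86, and the result would normally be called consistent.

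The main risk is accepting a partly active-controlled contrast as a reproduction of the placebo result. A reader might infer that sound methods are likely to fail at the 0.9 limit. The figures do not support that if the full TORCH effect carries over: it would need about 67% of controls on LABA+ICS, or about 80% on a mix of LABA+ICS and LABA. Failure becomes plausible only if the effect in routine care is weaker, for example 37% of controls if the true ratio is 0.85. All of this rests on the assumed equal efficacy of other LABA+ICS and on a share that the protocol does not report. The issue should be dealt with before the validation analysis, because it decides what a pass means.

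**What to change.** 1. In Exposures, state whether the objective 1 comparator is people not on FP/SAL or people on no maintenance inhaler, and use one term throughout. Reconcile this with the no-treatment wording for objectives 2 and 3 and with their reuse of the objective 1 selection steps.
2. Prespecify, whatever the first result shows, a second validation analysis in unexposed records with no LABA, ICS or LABA+ICS prescription in the 4 weeks before index. This is the look-back already used for FP/SAL. Apply the same two criteria and report it beside the broad comparison, labelled as a usual-care contrast.
3. Enter index-date use of each drug class in the propensity score, in addition to earlier use.
4. Report the share of controls on each class at index and during follow-up, so that readers can judge the dilution and the effect of later starts.

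**Cost.** Revised wording, one further analysis and a descriptive table. The protocol describes prescribing data as almost complete, so no new data source is needed. The restricted analysis has a smaller and more selected pool: at most about 44% can be lost before some TORCH participants go unmatched. It also leaves drugs started after index unaddressed, which is why item 4 is needed.

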Following this, we will select all patients in CPRD meeting the TORCH eligibility criteria specified above, and who also received treatment with FP/SAL (either on the date of eligibility or at a later date). From feasibility work, we anticipate ~12 000 eligible FP/SAL-treated patients (figure 2), some of whom may have multiple time periods of treated patient eligibility and therefore could contribute more than once to the initial pool of treated patients (figure 3). In contrast to the unexposed TORCH-eligible cohort, our initial approach will not involve matching participants of the exposed (to FP/SAL) TORCH-eligible cohort with participants from the TORCH trial, as this would negatively impact the ability to calculate propensity scores for receiving FP/SAL in step 5. Note that there will be overlap between those selected as untreated (in step 2) and as treated (in step 4). Approximately 90% of the step 4 treated patients will also have been eligible as step 2 untreated patients, as they will have had periods where they were not treated with FP/SAL and met the step 2 untreated eligibility criteria in addition to separate periods where they were treated with FP/SAL and met the step 4 treated eligibility criteria (figure 3). If a person is included in both the untreated step 2 and treated step 4 cohorts, they will be contributing different periods of their person-time to each cohort (pre-FP/SAL treatment for step 2 vs post-FP/SAL treatment for step 4), and this will be handled in the analysis by assigning different index dates for step 2 compared with step 4.

##### Step 5

We will combine the CPRD groups obtained in steps 3 and 4 (n~18 000, see note in step 4 relating to 90% overlap) and using their baseline characteristics will calculate propensity scores for receiving FP/SAL. The propensity score calculation will be based on a wide range of covariates (see the ’Statistical analysis' section for full details). Where a participant is contributing more than one treated time period record to the pool of exposed records (as described in step 4), baseline characteristics will be updated at the beginning of each treatment-eligible period. Multiple eligible treatment periods from a single person are then included in the propensity score model as if they came from different individuals. The variables selected for the score will then become the basis for propensity score modelling in objectives 2 and 3.

##### Step 6

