#### Objective 2: measurement of COPD treatment effects in patients excluded from trials

We will select separate cohorts of patients who have a valid COPD diagnosis in the CPRD^8^ and who would not have been eligible for inclusion in the TORCH trial (and therefore also not eligible for our objective 1) due to the following characteristics: (1) age >80 years OR (2) history of lung surgery OR (3) history of long-term oxygen therapy OR (4) evidence of drug/alcohol abuse OR (4) an asthma diagnosis at any time prior to inclusion OR (5) substantial comorbidity. In relation to substantial comorbidity, TORCH required people to be excluded from the trial if they had serious uncontrolled disease with a likelihood of causing death within 3 years. It is likely this criterion affected participant selection and led to a lower overall rate of death than originally anticipated, although we recognise this criterion is subjective. During objective 1, we will be able to select groups of people who were generally not included despite being eligible, most likely because of this subjective exclusion criterion. We anticipate this will be people with substantial comorbidity, for example, serious vascular disease. Status for such diseases is readily identified in both the CPRD data and in the TORCH baseline data. We will only be able to specify this criterion in detail after we have completed objective 1.

Participants for each of the objective 2 cohorts will be selected in a similar fashion to the objective 1 cohort, with the amended eligibility criteria specified above applied (ie, step 1 will be modified for selection of each of the objective 2 cohorts). As for objective 1, each participant will be allowed to have multiple FP/SAL exposed and unexposed eligibility periods in their record, as described in figure 3. In contrast to objective 1, there will be no matching of unexposed patients to TORCH patients, as we do not require a TORCH-analagous cohort for this analysis (ie, no step 3). All other selection steps will be as applied for objective 1, including the use of propensity score matching in order to obtain comparable unexposed and exposed groups for analysis.

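### Objectives 2 and 3 stratify on product strength as if it were dose, and the matching described for the drug as a whole does not ensure balance within those strata

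*Protocol article*

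**What the plan says.** All of this is in the protocol article.

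- **Dose variable (Exposures).** For objectives 2 and 3, "we will again use recorded prescribing information to determine the dose received". The next sentence reads "We will be reliant mostly on the strength of each individual drug, which is recorded automatically against each product", with completeness as the reason, since the GP does not have to enter strength. Then: "We will then be able to stratify analyses based on the dose prescribed". Every listed exposure is compared with no treatment.
- **Score (Objective 1, step 5).** The combined groups are taken and, "using their baseline characteristics will calculate propensity scores for receiving FP/SAL". No strength is named in the target of the score.
- **Carry-over.** Objective 2: "All other selection steps will be as applied for objective 1, including the use of propensity score matching". Objective 3: "the selection steps will be similar to objective 1, with modified criteria for step 1". In both, the matching to TORCH participants is dropped.
- **Objective 1 for comparison (Exposures).** "We will limit included patients to those receiving Seretide 500/50, the dose used in TORCH". No such restriction is stated for objectives 2 and 3.
- **Balance check (Methods of analysis).** Standardised differences are to be examined for the treated and untreated groups, with further model adjustment as a possibility. No check by strength is described.

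**The concern.** There are two separate problems.

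**Strength is not dose.** Amount received, amount prescribed and strength of the product are three quantities, and the Exposures section moves between them as if they were one. Strength becomes an amount prescribed only with the number of inhalations, and an amount received only with actual use as well. That strength is completely recorded does not make it a measure of dose.

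**The match is for any use of the drug.** A propensity score for receiving a drug makes the treated group as a whole comparable with its matched untreated group. It gives no assurance for a subset of the treated defined by something outside the score. In objective 1 this does no harm for FP/SAL, because only one strength enters. Once several strengths enter and results are split by strength, each stratum is such a subset.

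Selective choice of strength is plausible on the document's own account. It says of the 500/50 product that "this dose is the only currently approved dose for COPD in the UK" and concedes that some prescribing may not follow the licence. Objective 2 also admits patients with an asthma diagnosis. If strength follows risk, one stratum will look falsely worse and the other falsely better, in populations chosen because the trial has no result against which to check.

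**Working it through.** The plan states no figure on this point, so there is none to reproduce. The check has three parts. All inputs in parts 2 and 3 are assumptions.

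**1. Strength against amount received.** From the review of 30 FP/SAL starters (Handling measurement of adherence to medication):
- still treated at one year: 20/30 = 67%;
- of those, prescriptions suggesting at least 50% adherence: 15/20 = 75%;
- of those, at least 80% adherence: 8/20 = 40%, which is 8/30 = 27% of all starters.

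The sample is not split by strength, but coverage this varied means that a product's strength cannot stand for the amount received.

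**2. Exact example with the same true effect at both strengths.** Assume a true rate ratio of 0.75 at each strength, and two binary covariates, A (severity) and B (neutral), with four equally common cells. P(treated) is 0.4 for neither, 0.5 for A only, 0.5 for B only and 0.6 for both. The untreated rate is 0.5 per year, doubled by A. P(higher strength | treated) is 0.7 with A and 0.3 without. Cells with equal scores are matched to each other.

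- Treated weights (neither, A, B, both): 0.100, 0.125, 0.125, 0.150; total 0.500.
- Matched untreated rate by score: 0.50, 0.75 and 1.00. Mean = (0.100×0.50 + 0.250×0.75 + 0.150×1.00)/0.500 = 0.775.
- All treated: 0.75 × (0.050 + 0.125 + 0.0625 + 0.150)/0.500 = 0.75 × 0.775. Overall rate ratio 0.750, so the match works for the drug as a whole.
- Higher strength: weights 0.030, 0.0875, 0.0375, 0.105; total 0.260. Severe share 0.1925/0.260 = 0.74, against 0.275/0.500 = 0.55 in all treated. Rate = 0.75 × 0.22625/0.260 = 0.653.
  - Against all matched untreated: 0.653/0.775 = **0.842**.
  - Against own pairs (0.21375/0.260 = 0.822): **0.794**.
- Lower strength: weights 0.070, 0.0375, 0.0875, 0.045; total 0.240. Rate = 0.75 × 0.16125/0.240 = 0.504.
  - Against all matched untreated: 0.504/0.775 = **0.650**.
  - Against own pairs (0.17375/0.240 = 0.724): **0.696**.

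With weak inputs (A raises the rate by 1.2; P(higher) 0.6 against 0.4) the same steps give 0.763 and 0.736 against all matched untreated, and 0.757 and 0.743 with pairs kept. If strength does not depend on A, both strata return 0.750.

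**3. No drug effect, continuous severity.** Let X be standard normal, P(higher | X) = expit(gX), and event rate proportional to exp(bX).

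If the score is unrelated to X, the false rate ratio is E[expit(gX)e^{bX}] / (½·E[e^{bX}]) = 2·E[expit(g(X+b))] in the higher stratum, and 2 minus that in the lower:

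| g, b | higher | lower |
|---|---|---|
| 1, 0.5 | 1.20 | 0.80 |
| 1, 0.3 | 1.12 | 0.88 |
| 0.5, 0.5 | 1.12 | 0.88 |
| 0.5, 0.3 | 1.07 | 0.93 |

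Keeping pairs does not help here, because the pairs carry no information on X.

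Now let the treatment logit be aX + cZ, with Z an independent normal unrelated to outcome, and match on s = aX + cZ. The pair's expected rate is E[e^{bX} | s]. For g = 1, b = 0.5 with pairs kept:

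| score logit | higher | lower |
|---|---|---|
| 0.5X + 0.5Z | 1.08 | 0.88 |
| X + 0.5Z | 1.03 | 0.94 |
| X alone | 1.00 | 1.00 |

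For g = 0.5, b = 0.3 and X + 0.5Z, it is 1.01 and 0.98. If these same matched sets are instead compared with all matched untreated, the bias stays near its full size: about 1.14 to 1.20 and 0.80 in the strong case, and about 1.05 to 1.07 and 0.93 in the weak case.

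**The case against.** The best defence has five parts.

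- **Condensed text.** The article does not say how stratified analyses will be matched, and the sentence on stratification states what will be possible, not a specified analysis. Stratum-specific matching may be in a fuller document. This stands as a limit: use of an any-strength score in the strata is inferred from the steps carried over. Those steps are nonetheless the only ones described, and they were built for a single strength.
- **Qualifiers on strength.** The text says it relies mostly on strength, within recorded prescribing information, so quantity and directions are not ruled out, and completeness is a fair reason. This stands against making daily dose the primary variable, because directions may be missing. It does not justify calling strength the dose received.
- **Candidate covariates.** Lung function, prior COPD medication and healthcare use may enter the score, and matching is 1:1. This stands, and it is why the bias shrinks, possibly to nothing, when pairs are kept.
- **Balance checks.** Standardised differences and further adjustment are planned. They are described for the groups as a whole, where balance can be perfect while the strata are unbalanced.
- **Secondary role.** The stratification is secondary, and each drug is compared with no treatment. This stands and limits the weight of the point.

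A reader might also infer that objectives 2 and 3 reuse the objective 1 match. They do not: cohorts are selected and matched afresh, and the objective 1 variable list is only a starting point.

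**Conclusion.** The point holds in a limited form. The Exposures section treats strength as dose, which it is not, and the matching and balance checks described do not ensure comparability within strength strata. A false difference between strata arises only if strength depends on risk given treatment. With no drug effect and the assumed inputs above, its size runs from none to about 1.2 against 0.8. With a true ratio of 0.75 at both strengths, the false gap runs from 0.01 (0.757 against 0.743) to 0.10 (0.794 against 0.696) with pairs kept, and from 0.03 to 0.19 against all matched untreated. For scale, the protocol's window for agreement with TORCH is 0.65 to 0.9. The direction follows the channelling: if the higher strength goes to sicker patients, it looks less beneficial, and the reverse pattern reverses the sign.

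Three stronger readings are not supported:
- that the strata *are* unbalanced, since this depends on prescribing that the document does not report;
- that strengths of different molecules will be pooled on one scale, since the text speaks of each individual drug;
- that a dose-response test is planned, since none is stated.

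The overall objective 2 and 3 contrasts are not touched, nor is the validation against TORCH, which is limited to one strength.

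**What to change.** 1. Call the strata *prescribed strength*, and define them within drug or product. Drop the description of strength as the dose received.
2. For each stratum, fit the propensity score for that strength against untreated and re-match. Do not split a match made for any strength.
3. Report standardised differences within each stratum.
4. Report contrasts between strata as descriptive.
5. Where directions are recorded, use daily dose as a sensitivity analysis. Strength stays primary, which keeps the completeness that the protocol relies on.

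The cost is additional analysis and smaller matched sets in each stratum. The feasibility count of more than 2000 people over 80 in each exposure group is not split by strength, so stratum sizes should be counted first. No new data source is needed for steps 1 to 4.
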